### Blinding

It was not possible to blind participants and counsellors for the treatment allocation. Participants in the intervention groups attended group meetings with other participants from the same intervention group whereas participants in the control group did not. Since the primary outcome variables were self-reported, blinding was impossible. However, the researchers who performed the measurements were not aware of the treatment allocation of participants except for the counsellors who also performed part of the measurements.

### Description of the intervention

Like previous lifestyle physical activity intervention studies [24], the RSI@Work intervention is based on theoretical models of behaviour change, i.e. the Trans Theoretical Model (TTM) and the Precaution Adoption Process Model (PAPM). The TTM separates behaviour change into five discrete stages that are defined by a person's past behaviour and his or her plans for future action [25]. The PAPM resembles the TTM stages but introduces two new stages. These new stages distinguish between people who are unaware of an issue (Stage 1) and those who know something about an issue but never actively thought about it (Stage 2) [26]. Concepts of the PAPM and TTM, such as stage of change, awareness, self-efficacy and decisional balance, are used in the group meetings and applied to both the work style and the combined (work style and physical activity) intervention.

The interventions for the two intervention groups both consist of six interactive group meetings in a six-month period. All group meetings take place at the workplace, during work time (with permission of the employee) and under the supervision of a specially trained counsellor. The counsellors use standardized protocols that have been tested and improved during the pilot study. Four out of six meetings are large group meetings with maximally 10 participants. Two out of six meetings are small group meetings with maximally four participants. The goal of all group meetings is behavioural change with regard to physical activity and/or work style. The goal of the large group meetings is to provide general information and to raise awareness about work style and/or physical activity, and to discuss and find solutions for general barriers with regard to behavioural change. The goal of the small group meetings is to provide participants with tailored advice based on their stage of change with regard to work style and/or physical activity. In addition, solutions for individual barriers with regard to behavioural change are discussed.

The counsellor provides the work style part to both intervention groups and the physical activity part to the 'work style and physical activity group' only. The group meetings of the 'work style and physical activity group' are separate from the group meetings of the 'work style group'.

#### Group meeting 1 (large group meeting)

*Work style *(1 hour). The goal is to provide general information about neck and upper limb symptoms and its known risk factors. The following risk factors are discussed: workplace adjustment and body posture, static workload and insufficient breaks, high workload and work stress. Finally, information is provided about the study and the next group meetings. *Physical activity *(30 minutes). The goal is to provide information about the importance of physical activity in the prevention or reduction of neck and upper limb symptoms and to raise awareness about participants' own physical activity pattern. The dynamic model of workload is presented to explain the role of physical inactivity in the development of neck and upper limb symptoms. The counsellor explains the Dutch guidelines (similar to ACSM/CDC guidelines) for regular physical activity (i.e. engaging in moderate intensity physical activity for at least 30 minutes on at least five days of the week) and strenuous physical activity (i.e. engaging in strenuous intensity physical activity for at least 20 minutes on at least three days of the week). Participants are requested to check whether or not their own daily physical activity pattern meets these guidelines. The counsellor stresses the importance of active commuting and sufficient physical activity at work and during leisure time. Participants are asked to make a physical activity plan, to act according to this plan and to write down perceived barriers that prevented them from being physically active as planned. Participants are also asked to think about barriers that might prevent them from being sufficiently physical active in the future. Workers who are sufficiently active at the start of the study according to the general guidelines are encouraged to improve their physical activities by spending more time on activities that involve the upper extremities or by becoming more active at work.

#### Group meeting 2 (large group meeting)

*Work style *(1 hour). The primary goal is to provide the general guidelines for workplace adjustment and body posture (Table 1) and to make participants aware of their own workplace and body posture. The second goal is to provide information about the importance of breaks and exercise reminder software and to stimulate the use of it. All participants get access to this software. *Physical activity *(30 minutes). The goal is to discuss the physical activity plans and the perceived and expected barriers. Groups are stimulated to find solutions for reported barriers. Participants who already meet the physical activity guidelines at baseline are encouraged to explain to others how they manage to be sufficiently active and cope with barriers. Participants who fail to perform their planned activities are asked to adjust their physical activity plan in order to make it more feasible. At the end of the meeting all participants receive an elastic band with exercises for the upper extremities.

#### Group meeting 3 (small group meeting)

*Work style *(30 minutes). The goal of this meeting is to bring the guidelines for workplace adjustment and body posture into practice. In a small group, participants visit each other's workplace. The counsellor will ask participants to judge and adjust each workplace according to the guidelines (Table 1). If necessary, the counsellor makes some final adjustments to the workplace at the end of the meeting. Furthermore, the use of break and exercise reminder software is discussed. The counsellor checks with the participants whether the software has been installed properly, whether the software has been used and discusses the experiences. The counsellors advice will be based on the stage of change of participants. If the workplace has not been adjusted or the software has not been used, barriers will be discussed as well as the importance of workplace adjustment and the use of breaks and exercise reminder software. If the workplace has been adjusted and software has been used, the counsellor encourages this behaviour and will ask participants about the use of the exercises that are provided by the exercise reminder software. *Physical activity *(15 minutes). If participants have not decided to change their physical activity behaviour, the counsellor will raise awareness and stress the positive aspects of physical activity and the risk of physical inactivity. If participants have decided to change their physical activity behaviour but have not started yet, the counsellor will discuss (individual) barriers together with the other participants. Furthermore, the counsellor will encourage participants to adjust their physical activity plan in order to make it more feasible. If participants started to become more physically active the counsellor will encourage this behaviour and discuss possible future barriers.

#### Group meeting 4 (large group meeting)

*Work style *(1 hour). The first goal is to provide information about high workload and work stress and the relationship with neck and upper limb symptoms. The second goal is to teach participants how to recognize work stress. The counsellor discusses biological (e.g. insomnia, headache, high blood pressure), behavioural (e.g. excessive smoking or drinking behaviour, restlessness) and emotional indicators of work stress (e.g. concentration difficulties, feelings of insecurity or guild, amnesia). The third goal is to raise awareness about general and individual risk factors for work stress during a brainstorm session. The counsellor provides each participant with three to five post-it stickers and asks them to write down a factor on each post-it sticker that he or she associated with work stress (e.g. too much work, unclear task descriptions). The most frequently reported risk factors are discussed. *Physical activity *(30 minutes). The goal is to discuss the physical activity plans and the experienced and expected barriers. Furthermore, the counsellor discusses the process of behavioural change.

#### Group meeting 5 (small group meeting)

*Work style *(30 minutes). The goal of this meeting is to discuss individual risk factors for work stress raised by participants. The group is stimulated to find solutions for risk factors and to discuss ways of coping with work stress as well as barriers to cope with work stress. In addition, the counsellor discusses the use of breaks and exercise reminder software, body posture and workplace adjustment. *Physical activity *(15 minutes). The goal is to evaluate participant's physical activity pattern and to give supplementary advice if necessary.

#### Group meeting 6 (large group meeting)

The goal is to summarize and evaluate all group meetings and to discuss how to attenuate behavioural changes.

Participants in the control group do not attend any of the group meetings. If they visit their occupational physician for neck and upper limb symptoms they receive usual care.

### Co-intervention and compliance (dropout)

Although all workers who reported to be under treatment of a doctor or (physical) therapist for complaints in the neck, shoulders arms, wrists and/or hands at the start of the study were excluded for participation, we allowed participants to visit a doctor or (physical) therapist during the study. In order to adjust for co-interventions participants were asked to report all actions taken to reduce their neck and upper limb symptoms (e.g. visiting a doctor or taking medication). Two estimates of compliance are used in our study, i.e. 1. compliance to the group meetings and 2. compliance to the study. During each group meeting the counsellor checks the presence of each participant.

### Contrast between intervention and usual care

In May 2003 the Dutch guidelines for the occupational health management of workers with complaints in arm, shoulder and neck were published [27]. According to these guidelines the occupational physician should advice workers with neck and upper limb symptoms to keep working but to discontinue tasks that cause intense pain. Furthermore, therapies that activate workers are preferred above usual physiotherapy. In case of bad workplace ergonomics, the guidelines recommend to improve the workplace in combination with personalized interventions. In case of stress, the guidelines recommend changes in work organization and work situations. If the worker has non-realistic cognitions the guidelines recommend the occupational physician to explain the multifactorial origin of arm, shoulder and neck symptoms and its good prognosis. If necessary, workers can be send to a psychologist. In case of sickness absence, workers will be stimulated to resume their work gradually based on a time contingent schedule of which the length is dependent on the seriousness of the complaints and the workload.

Although the RSI@Work intervention is based on the Dutch guidelines for the occupational health management of workers with complaints in arm, shoulder and neck, it differs from the guidelines with regard to three aspects. First of all, many computer workers with neck and upper limb symptoms who are not on sick leave do not visit their occupational physician. At baseline only 13.5% of the RSI@Work participants had visited their occupational physician for neck and upper limb symptoms. As a consequence many participants in the control group of this study will not receive the treatment as described by the guidelines for occupational health management. The participants in the intervention groups, on the other hand, will all be invited to attend the group meetings. Secondly, RSI@Work participants are not treated by a doctor or therapist but are guided by a counsellor. During the group meetings, the focus is on behavioural change instead of on symptoms. Participants of the RSI@Work study are offered knowledge and methods to reduce their neck and upper limb symptoms by themselves. For instance, they learn to adjust their own workplace by themselves which is in contrast to general occupational health management, where workplaces are often adjusted by occupational therapists. Although some companies provide workers with information about the adjustment of their workplace, workers often feel uncertain about changing their workplace by themselves. In addition, participants in the RSI@Work intervention groups are stimulated and guided in using breaks and exercise reminder software. In some Dutch companies breaks and exercise reminder software is available but guidance is often lacking. Furthermore, participants in the combined (work style and physical activity) intervention are stimulated to increase their physical activity, not by offering a training protocol but by helping them to find ways to incorporate physical activity into their daily lives. Although some large companies offer fitness facilities, this form of physical activity is not attractive for all workers. Training protocols and physical activities that do not fit the worker are believed not to be effective on the long-term. The third important difference between the RSI@Work intervention and usual occupational health management is the fact that the RSI@Work intervention consists of six group meetings. This provides the opportunity for feedback and to discuss positive and negative experiences with the new learned behaviours. In general, usual occupational health management is based on individual advice and treatment.

### Measurements

All outcome variables, except for degree of recovery and body height, will be assessed three times: prior to the start of the intervention (T0), at the end of the six month intervention (T1) and 12 months after the start of the intervention (T2). Degree of recovery is assessed at T1 and T2 and body height is measured at baseline only.

#### Primary outcome variables

1. Degree of recovery from neck and upper limb symptoms assessed using a 7-point scale ranging from "much worse" to "completely recovered" compared to baseline.

2. Pain intensity (current pain, average pain and worst pain in the past four weeks), assessed using an 11-point numerical rating scale ranging from 0 "no pain" to 10 "worst pain ever" [28].

3. Disability assessed using an 11-point numerical rating scale [28]. Change in ability to work in the past four weeks is assessed with Von Korff scales ranging from 0 "no change" to 10 "extreme change". Interference of pain on daily activities in the past four weeks is assessed with Von Korff scales ranging from 0 "no interference" to 10 "unable to carry on any activities".

4. The Dutch musculoskeletal questionnaire [29] is used to assess the six month prevalence of symptoms (pain, stiffness, tingles or numbness) in the neck, right shoulder, left shoulder, right arm, left arm, right wrist, left wrist, right hand and left hand in the past six months. In the same questionnaire, participants report the number of days with neck and upper limb symptoms in the past 6 months (no symptoms, 1–7 days, 8–30 days, 31–90 days, 91–180 days) and the past week (no symptoms, 1 day, 2–3 days, 4–7 days).

5. Number of months without neck and upper limb symptoms in the past six months (0–6 months).

Degree of recovery, pain intensity, number of days with neck and upper limb symptoms and disability will be assessed separately for the neck shoulder region and the arm/wrist/hand region.

#### Secondary outcome variables

1. Physical activity is assessed by means of the validated Short Questionnaire to Access health enhancing physical activity (SQUASH) [30]. The SQUASH questionnaire contains questions about activities in the following four domains: 1) commuting activities (i.e. walking and cycling), 2) activities at work and school, 3) household activities, and 4) leisure time activities (i.e. walking, cycling, gardening, chores, and sports).

2. Body posture and workplace ergonomics during computer work (self reported). Participants rate themselves on the tendency of forward chin movement relative to the trunk in the direction of the computer screen (yes/no), using a document holder (yes/no), location of documents while working with them (right or left from keyboard, behind keyboard, in front of keyboard), keyboard height compared to elbow height (keyboard above elbow height, keyboard at or below elbow height), the tendency to work with raised shoulders (yes/no), keyboard flat on the desk (yes/no), use of mouse (yes/no), left handed (yes/no), hand that controls the mouse (left/right/both), convenient body posture while working with the keyboard and the mouse (yes/no).

3. Body posture and workplace ergonomics during computer work (observed). The following aspects will be observed, using a checklist while the participant is working: position of the participant in relationship to the position of the computer screen (rotation < 10°, rotation ≥ 10°), rotation of keyboard compared to table edge (rotated < 10°, rotated ≥ 10°), rotation of the neck (rotated < 20°, rotated ≥ 20°), height of the computer screen (top of screen far beneath eye height, at eye height, above eye height), viewing distance (shortest distance between the eyes and the computer screen) using a measuring tape, posture of the back while seated (straight/not straight), back supported up to shoulder blades (yes/no), body posture more or less symmetrical (yes/no), support of the elbows while typing (yes/no), ulnar deviation of wrists while typing (yes = ≥ 20°, no = < 20°), lower arm continuously supported (at least 50%) while working with the mouse (yes/no), ulnar wrist deviation while working with the mouse (yes = ≥ 20° or < -5° ; no = < 20° and > -5°).

4. The use of breaks and exercise reminder software and the number of breaks will be assessed by questionnaire.

5. Extrinsic effort and reward (esteem reward, status control and monetary gratification) and need for control, assessed by the short version of the Effort-Reward imbalance questionnaire [31].

6. Decision authority, estimated with the Job Content Questionnaire [32].

7. Phase of behavioural change with regard to physical activity and work style (1. coping with work-related stress, 2. sufficient breaks, and 3. body posture and workplace adjustment), assessed with a questionnaire based on the Trans Theoretical model [33] and the Precaution Adoption Process Model [26].

8. Cardio respiratory fitness, estimated using the validated UKK walk test [34,35]. A short medical questionnaire is used in order to exclude participants from the UKK walk test due to medical reasons.

9. Maximum grip strength, measured using the Jamar hand dynamometer [PGB Active Living, 's-Hertogenbosch, the Netherlands] while the participant is standing with the shoulder in 90° flexion and the arm in full extension.

10. Health care use. At baseline participants were asked whether or not they ever sought medical help for neck and upper limb symptoms. In addition, they were asked to indicate which health care provider(s) they visited. At both follow-up measurements participants were asked again whether or not they sought medical help for neck and upper limb symptoms in the past six months and which health care provider(s) they visited.

### Cost data

Cost effectiveness analyses will be conducted from the employer's perspective. Absenteeism and worker productivity will be based on self-reports using the Health and Performance Questionnaire (HPQ) [36]. Absenteeism will also be assessed by company records.

### Data analysis

Intention-to-treat analyses will be used to estimate the effect of the intervention. Multilevel analyses will be used to investigate differences in recovery and changes in outcome variables between the intervention groups and the control group after six months and one year of follow-up. Multilevel analyses are used in order to adjust for possible dependency between observations from the same company.

Cost-effectiveness ratios will be calculated by dividing the difference between the mean costs by the difference in the mean effects in the primary outcome variables. Bootstrapping will be used to calculate the confidence intervals for the cost-effectiveness ratios. Ratios will be graphically presented on a cost-effectiveness plane. Furthermore, acceptability curves will be calculated for both interventions showing the probability of being cost-effective a specific ceiling ratio.

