### Treatment allocation

An independent statistician prepared the randomisation by using a computer-generated randomisation. To prevent unequal randomisation, workers were pre-stratified by company and baseline sports participation assessed with the baseline questionnaire. Furthermore, block randomisation with blocks of three was used. The researchers prepared the envelopes containing the allocation to the intervention group and made two boxes with envelopes for each company. The first box contained the envelopes for workers who participated in sports activities (i.e. at least twice a week during at least 20 minutes at a moderate intensity level). The second box contained the envelopes for workers who did not participate in sports activities. Directly after the baseline measurements were completed the researchers opened the envelope and informed the worker about the group allocation. Workers who did not participate in the baseline measurements but sent their completed questionnaire and informed consent by post were randomised at the VU university medical center and informed about their treatment allocation by phone or by email.

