### Sample size and participant flow

The main primary outcome variable in this study is self-reported recovery. The intervention will be considered successful if recovery from work-related neck and upper limb symptoms (i.e. completely recovered or much recovered) is 20% higher in the intervention group than in the control group. The number of participants in each group needed to detect a difference in recovery of 20% between the intervention group and the control group was ± 80, with α = 0.05 (two sided) and β = 0.20. This number was based on our expectation that recovery would be 80% in the intervention group and 60% in the control group. However, since we expected a loss-to-follow-up of 40%, ± 135 workers were needed in each group at baseline. Based on our pilot study we expected that 6.25% of our source population would participate in the study, which brings the minimum number of workers that needed to be invited for participation at 6480 workers. Figure 1 shows that approximately 8000 workers were invited to participate and that 466 workers were randomised into the trial.

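### Outcomes other than recovery are to be analysed as changes with only company named in the model; adjusting for baseline value and sports stratum would gain precision at almost no cost

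*Protocol article*

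**What the plan says.** The Data analysis section plans intention-to-treat multilevel analyses that will "investigate differences in recovery and changes in outcome variables" between the intervention groups and the control group at six and twelve months. The reason given for the multilevel model is dependence between workers of the same company. Neither the baseline value nor sports participation is named as a covariate.

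Four other places bear on this:

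- **Treatment allocation:** "workers were pre-stratified by company and baseline sports participation assessed with the baseline questionnaire". There were two strata; company is the one that reappears in the analysis.
- **Measurements:** every outcome except degree of recovery and body height is assessed at T0, T1 and T2. Recovery is assessed at T1 and T2 only.
- **Sample size and participant flow:** "The main primary outcome variable in this study is self-reported recovery".
- **Secondary outcome variables, item 10 (health care use):** "At baseline participants were asked whether or not they ever sought medical help for neck and upper limb symptoms". Both follow-up questionnaires ask instead about the preceding six months.

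**The concern.** The article names the response variable, and for everything but recovery it is a change. That covers pain intensity, disability, days with symptoms and months without symptoms (four of the five listed primary outcomes), plus the secondary outcomes.

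For a continuous outcome, an unadjusted change score subtracts the whole baseline value, although the follow-up value usually tracks it only in part. The excess adds noise and leaves the comparison open to chance baseline imbalance. Adjusting the follow-up value for baseline subtracts only the predictive part. At stake are wider confidence intervals than the collected data allow.

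The sports stratum is a second, smaller matter. An analysis that ignores a balanced stratum does not credit the balance it bought. Sports participation plausibly predicts physical activity and fitness, since the SQUASH questionnaire itself covers sports.

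Health care use is a third. Its baseline and follow-up questions cover different periods, so a like-for-like change cannot be formed.

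**Working it through.** **1. The plan's own figure.** The inputs, from the sample size section, are "recovery would be 80% in the intervention group and 60% in the control group" with "α = 0.05 (two sided) and β = 0.20".

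- Pooled formula: n = [1.96·√(2·0.7·0.3) + 0.842·√(0.8·0.2 + 0.6·0.4)]² / 0.2², which gives 82 per group. The unpooled form gives 78.5 and the arcsine form 80.3. The stated ±80 is reproduced.
- Attrition: "we expected a loss-to-follow-up of 40%, ± 135 workers were needed in each group at baseline". 80/0.6 = 133.3, so 134, which agrees.
- Invitations: 3·135/0.0625 = 6480, which agrees.
- Recruitment: "466 workers were randomised into the trial". 466/3 = 155.3 per group, and 155.3·0.6 = 93.2 after 40% loss. Power for recovery is then about 85%.

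This calculation concerns recovery, which has no baseline value, so nothing in step 2 alters it.

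**2. Change score against baseline adjustment, continuous outcomes.** Let s0 and s1 be the baseline and follow-up SDs and r their correlation.

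- Variance of an unadjusted change: s0² + s1² − 2·r·s0·s1
- Variance after baseline adjustment: s1²·(1 − r²)
- Difference: (s0 − r·s1)², which is never negative

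The direction therefore does not depend on the SDs, but the size does. With s0 = s1 = 1 the two variances are 2(1 − r) and 1 − r², and the ratio is (1 − r²)/[2(1 − r)] = (1 + r)/2.

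The article gives no SD or correlation, so r below is assumed. The last two columns take an effect that has 80% power at 80 per group under baseline adjustment. The 80 is only a yardstick borrowed from the recovery calculation.

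| assumed r | adjusted / change variance | SE, change / adjusted | power as unadjusted change, 80 per group | n per group to restore 80% |
|---|---|---|---|---|
| 0.3 | 0.65 | 1.24 | 62% | 124 |
| 0.5 | 0.75 | 1.155 | 68% | 107 |
| 0.7 | 0.85 | 1.085 | 73% | 95 |
| 0.8 | 0.90 | 1.05 | 76% | 89 |

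The last column is 80/[(1 + r)/2] rounded up; for example, 80/0.75 = 106.7, so 107. Below r = 0.5 the change variance 2(1 − r) exceeds 1, so an unadjusted change is then less precise than ignoring baseline altogether.

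**3. Sports stratum.** If the stratum explains a share R² of outcome variance, the residual variance falls by that share. For an assumed R² of 1% to 10% the factor is 0.99 to 0.90. The reported standard error is then too large by 1/√0.99 = 1.005 to 1/√0.90 = 1.054.

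**4. Health care use.** The Measurements section counts it among outcomes assessed three times, and the Data analysis section speaks of changes in outcomes. Item 10 asks about lifetime use at baseline and six-month use afterwards, so subtracting one from the other does not measure a change in use.

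**The case against.** The strongest objection is that the covariate gap is read from silence. The section is a short summary in a journal article, and it is not a full list of model terms: the section on co-intervention and compliance mentions adjusting for co-interventions, which the Data analysis section does not repeat. A change score modelled with baseline as a covariate gives the same treatment estimate as an adjusted follow-up value. If the full plan does that, the efficiency loss disappears.

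This stands in part. A reader might infer that the plan rules out baseline or stratum adjustment, and the article does not say so. It does, however, state change as the response and name company alone, so the stated method can be improved as written.

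Further limits on the point:

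- The (1 + r)/2 ratio needs a continuous outcome, equal SDs and an unadjusted change. It does not apply to banded symptom days, yes/no posture items, stage of change or health care use. If selection on symptoms made the baseline SD smaller than the follow-up SD, the gain could be smaller, vanishing at s0 = r·s1.
- A reader might infer bias or false positives from the missing stratum. Omitting a balanced stratum generally makes tests conservative, and company is already in the model.
- A reader might infer that the health-care-use comparison would be driven by the differing recall periods. Both arms answer the same questions, so under randomisation the mismatch is expected to cancel between arms. It adds noise and makes within-arm change uninterpretable.

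**Conclusion.** The point holds as an efficiency improvement for outcomes other than recovery. For continuous outcomes, baseline adjustment would bring the variance to between 0.65 and 0.90 of that of an unadjusted change score. That range rests on assumed correlations of 0.3 to 0.8, equal SDs at both times, and a change analysed without its baseline as covariate. The sports stratum adds a probably small gain, resting on an assumed R² of 1% to 10%.

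It would be tempting to conclude that the trial's main result or its sample size is compromised. The article does not support that. Recovery is compared as a difference, is rated by the participant against baseline, and is measured only at follow-up. The ±80 and ±135 figures stand.

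The health-care-use mismatch is a real inconsistency between the questions asked and an analysis of change, confined to one secondary outcome.

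**What to change.** In the Data analysis section, state that:

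1. For outcomes measured at baseline, the T1 and T2 values are modelled with their own baseline value and the sports stratum as covariates, with company kept as a level of the multilevel model.
2. The recovery model includes the sports stratum alongside company.
3. Health care use is compared between arms on the follow-up answers, with lifetime use at baseline as a covariate and not as a change.

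No new data are needed: the sports stratum and the questionnaire baselines come from the baseline questionnaire completed before randomisation. The wording should be settled before group comparisons are seen.

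There is one small cost. Workers who skipped the baseline measurements were still randomised on questionnaire and consent (Design and study population; Treatment allocation). They lack baseline fitness, grip strength and workplace observation, so models for those outcomes need a simple stated rule for missing baseline values.
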